### End Points

Overall response rate (ORR) is the primary end point. The secondary end points are PFS, OS, disease control rate, safety, and patient-reported outcomes, including the results of the European Organization for Research and Treatment of Cancer Quality of Life Questionnaire–Core 30 and Quality of Life Questionnaire–Lung Cancer Module 13. MRI or CT examinations will be administered at the start point, week 3, and each 6 weeks following. According to the RECIST1.1 and the National Cancer Institute Common Terminology Criteria for Adverse Events (version 5.0), tumor response and adverse events will be evaluated and recorded during therapy and within 28 days after the last dose, respectively. Telephone checks will be conducted every 3 months until the end of the trial, death, or loss to follow-up.

After illness progression or withdrawal from the trial’s treatment, the use of anticancer medication will be recorded. ORR is the proportion of enrolled patients with a CR or PR based on imaging. PFS is the length of time between enrollment and the occurrence of disease progression. OS is the duration between enrollment and death.

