### Eligibility Criteria

The inclusion criteria are as follows: (1) age 18-75 years; (2) histologically or cytologically confirmed NSCLC; (3) liver metastases confirmed by abdominal imaging, such as computerized tomography (CT) or magnetic resonance imaging (MRI); (4) negative for epidermal growth factor receptor and anaplastic lymphoma kinase, as assessed by polymerase chain reaction or next-generation sequencing; (5) Eastern Cooperative Oncology Group performance status 0-2; (6) at least 2 measurable lesions according to Response Evaluation Criteria in Solid Tumors 1.1 (RECIST1.1) guidelines ; (7) asymptomatic (identified as being without significant symptoms at baseline, judged by the investigator as not requiring steroids and/or local treatment) or symptomatically stable brain metastases (without significant symptoms after local treatment, such as RT, and at least 7 days free from steroids and/or anticonvulsant therapy at the time of enrollment); (8) requirement for immunotherapy; (9) liver metastases (confirmed by imaging and multidisciplinary tumor board consultation) that can be treated with HIFU; (10) agreement to use effective contraception during the beginning of the trial and 90 days after the dose; (11) written informed consent.

Exclusion criteria for patients are as follows: (1) mixed lung cancer, including neuroendocrine tumors or sarcoma; (2) history of other malignancies within 5 years; (3) effusions of the third space that cannot be drained or otherwise treated; 4) severe interstitial pneumonia or severe diffusion dysfunction; (4) liver function with Child-Pugh grade C; (5) history of immunodeficiency disease necessitating long-term treatment with glucocorticoids; (6) history of acute cardiovascular or cerebrovascular disorders, including acute cerebral infarction and acute coronary syndrome, within the last month; (7) pregnant or lactating women; (8) life expectancy 3 months or less.

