### Intervention

Eligible patients will receive HIFU on liver metastases and PD-1 blockade therapy. Given the potential immunomodulation effect of HIFU, ablation of metastatic liver lesions was planned to take place within no more than 7 days of immunotherapy. The PD-1 blockade was injected repeatedly every 3 weeks for 6 cycles. The combination of immunotherapy and ablation was administered once in week 1. The study schema provides a comprehensive summary (Figure 2). Patients who are considered to have obtained clinical benefits, including a complete response (CR), partial response (PR), or having achieved stable disease (SD), will be allowed to continue PD-1–blocking medicines (every 3 weeks) for up to 2 years beyond the end of the trial. Patients with progressive disease will exit the trial or undergo re-ablation with HIFU according to their choice. Re-ablation will be performed in liver metastases without changing the immunotherapy regimen, and the efficacy will be evaluated 3 weeks later. If the treatment outcome is progressive disease, the patient will be withdrawn from the study. If the outcome is SD, PR, or CR, the patient will be treated and followed up. The standard PD-1 blockade treatment plan for advanced lung cancer with liver metastases will be used, as determined by the investigators and based on clinical guidelines.

Whole blood, plasma, archived cancer tissue, and tumor biopsies will be taken for exploratory research. Given the stability and availability of the test, peripheral blood will be obtained for lymphocyte subsets and the levels of 12 cytokines (tumor necrosis factor [TNF]-α, interleukin [IL]-6, IL-10, IL-17, interferon [IFN]-α, IL-1β, IL-2, IL-5, IL-8, IL-12P70, IFN-γ, IL-4) will be measured before and after HIFU treatment. Tumor biopsy tissue will be embedded in paraffin and analyzed for immune cell infiltration and PD-L1 expression. This information will help us determine whether the medication modifies the diversity of immune response and whether these changes are reflected in the blood. This could aid in the selection of predictive biomarkers for patients in future trials by connecting immunological alterations to clinical symptoms.

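### Adverse events starting more than 28 days after the last dose have no stated route into the safety data, although patients stay in telephone contact and safety is a secondary end point

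*Protocol article*

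**What the plan says.** The protocol article, End Points, lists safety among the secondary end points. It then says that "tumor response and adverse events will be evaluated and recorded during therapy and within 28 days after the last dose, respectively". The limit that matters here is "within 28 days after the last dose". No other section gives a longer period for serious or immune-related events.

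The same section keeps patients in contact after treatment: "Telephone checks will be conducted every 3 months until the end of the trial, death, or loss to follow-up". It does not say what is asked at these checks. It names one item for the period after treatment: "After illness progression or withdrawal from the trial’s treatment, the use of anticancer medication will be recorded".

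Under Intervention, dosing is given as "The PD-1 blockade was injected repeatedly every 3 weeks for 6 cycles", and HIFU timing as "ablation of metastatic liver lesions was planned to take place within no more than 7 days of immunotherapy"; the Abstract places HIFU 1 week before the first dose. Patients with clinical benefit may continue PD-1 blockade beyond the six cycles. For the others, "Patients with progressive disease will exit the trial or undergo re-ablation with HIFU according to their choice".

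One further period appears under Eligibility Criteria, as a condition of entry: "agreement to use effective contraception during the beginning of the trial and 90 days after the dose".

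**The concern.** The trial tests a combination whose safety, as its own Discussion admits, is not yet fully determined. The Introduction says that checkpoint blockade in immunologically cold tumors can bring excessive adverse reactions, and that HIFU is meant to turn such tumors immune-reactive. Immune-related toxicity is therefore an outcome the plan has its own reasons to watch.

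Against that, the recording window ends 28 days after the last dose, only 7 days longer than one 21-day dosing interval. Contact goes on after that, but nothing says toxicity is asked about. If staff follow the text as written, a serious event on day 40 in a patient who stopped for progression need not be recorded. The safety summary would then be incomplete in a way that its reader could not see. The patient is in the safety set, but the event is not in the data.

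**Working it through.** The plan states no figure to reproduce here. The check is a comparison of the stated rules plus calendar arithmetic.

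**Reading the window.** The word *respectively* in the End Points sentence can be taken in two ways:
- It pairs each outcome with its grading standard. Both outcomes are then recorded during therapy and for 28 days afterwards.
- It pairs each outcome with a period. Tumor response is then recorded during therapy, and adverse events in the 28 days after the last dose. Taken literally, this leaves out adverse events during therapy, which cannot be meant.

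The sensible reading is recording during therapy and to day 28. Under either reading, recording closes at day 28.

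**Inputs.**
- Dosing every 21 days for 6 cycles (Intervention)
- HIFU 7 days before the first dose (Abstract; also the upper limit under Intervention)
- Window of 28 days after the last dose (End Points)
- 30 patients (Statistical Analysis)

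**Length of coverage.** Let day 0 be the first dose. With k doses, the last dose falls on day 21 × (k − 1) and the window closes 28 days later. HIFU is on day −7, so add 7 to count from HIFU.

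| Doses received | Last dose (day) | Window closes (day) | Days after HIFU |
|---|---|---|---|
| 1 | 0 | 28 | 35 |
| 2 | 21 | 49 | 56 |
| 6 | 105 | 133 | 140 |

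Patients who continue beyond six cycles are covered for longer, because the window moves with the last dose.

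**Effect of recording to 90 days after the last dose.** The extension is 90 − 28 = 62 days. After one dose, recording would close on day 90 instead of 28. After six cycles it would close on day 105 + 90 = 195 instead of 133.

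**Stated routes for an event after day 28.**
- Routine recording: closed
- Telephone check: purpose not stated
- Collection after progression or withdrawal: anticancer medication only

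None is a stated route for an adverse event.

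**What an uncollected rate would mean (illustration only).** The documents give no rate of late events, so the rate p is an assumption. In 30 patients the expected number is 30p, and the chance of at least one is 1 − (1 − p)^30.

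| Assumed p | Expected events | Chance of at least one |
|---|---|---|
| 2% | 0.6 | 45% |
| 5% | 1.5 | 79% |
| 10% | 3.0 | 96% |
| 15% | 4.5 | 99% |

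Nothing in the documents helps to choose a row.

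**The case against.** A reader might infer that the plan contradicts itself: that it treats exposure as lasting 90 days, observes only 28 of them (31%), and so misses late immune toxicity. The documents do not support that.

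- The 90 days is a contraception condition. No section calls it an exposure or at-risk period, and the two periods serve different purposes and need not match. It shows that the plan takes some precaution beyond day 28, no more.
- The documents give neither the timing nor the rate of late immune events, so it is not shown that any event is missed. The content of the telephone checks is unstated, which neither includes nor excludes adverse events.
- One event in 30 patients is 3.3 percentage points, but that is the weight of any event in a trial of this size, not an estimate of the loss. The safety analysis is descriptive and has no threshold that a late event could cross.
- The window follows the last dose, so patients on long treatment are observed for a long time. Not every patient who progresses leaves early: some may choose re-ablation with the immunotherapy regimen unchanged.
- A condensed article may leave call content and longer follow-up of serious events to the full protocol.

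All of this stands as a limit on the claim. The last point does not remove it. The article is not silent on the window: it states a cut-off and gives no exception. If the full protocol follows serious or immune-related events for longer, the published statement should say so.

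**Conclusion.** The point holds as a gap in stated collection. Recording ends at day 28 after the last dose, contact continues, and later serious or immune-related events have no stated route into a secondary end point. The gap comes soonest for patients who stop after one or two doses, whose recording closes on day 28 or 49 from the first dose, against day 133 after six cycles.

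The number of events affected cannot be given. The calendar figures assume dosing on schedule and HIFU 7 days before the first dose; with a shorter interval, coverage after HIFU is shorter still. The conclusion assumes that the article's window is the one in force. It does not rest on the contraception clause, and it leaves the primary end point, sample size, alpha and power unchanged. It is a cheap improvement to the completeness of the safety data.

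**What to change.** In End Points:

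1. Reword the sentence containing *respectively* so that tumor response and adverse events each have their own stated period. Say plainly that adverse events are recorded during therapy and to 28 days after the last dose.
2. Keep that window for all adverse events. Add recording of serious and immune-related events to 90 days after the last PD-1 dose or the last HIFU session, whichever is later. The present window is tied to the dose only, although HIFU may be repeated.
3. Collect these events retrospectively at the first existing telephone check on or after day 90. The article does not tie the calls to the last dose, so the form should ask for onset dates.
4. State that this includes patients who stopped for progression. The article says such patients may exit the trial, so it should be explicit that they are still called.
5. Flag events that start after new anticancer therapy, which is already recorded, and report them separately.

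The cost is a few more questions at a call that is already planned, with no added visit or procedure. The downside is that some late events will be confounded by later therapy or recalled imprecisely. With 6 participants recruited by April 2024, a change made at about that stage would cover most of the planned 30.

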Nevertheless, a substantial proportion of patients fail to benefit from immunotherapy, particularly those with lung cancer liver metastases [5]. The existence of baseline liver metastases in patients with lung cancer has been connected with a reduced response to immunotherapy. In the Checkmate 017 and Checkmate 057 trials, the 3-year overall survival (OS) rate for subgroups of patients with lung cancer liver metastases treated with pembrolizumab was 8%, as compared to a 3-year OS of 17% across all enrolled patients [6]. Similarly, in the Keynote 001 trial among patients with non–small cell lung cancer (NSCLC), liver metastasis was linked with a decreased treatment response and shorter progression free survival (PFS) in comparison to patients without liver metastasis [7]. In patients with NSCLC with similar PD-L1 expression, tumor burden, and mutational burden, the presence of liver metastases was linked with reduced OS regardless of age, sex, or treatment modality. [8,9]. Liver metastases are independently associated with a poorer response to immunotherapy, primarily due to the liver’s unique immunosuppressive microenvironment [10]. The liver processes a vast array of harmless dietary antigens daily, necessitating a state of immune tolerance [11]. Metastatic lesions in the liver further enhance this immunosuppressive milieu. Liver metastases highly express integrin receptors, including cluster of differentiation [CD] 44 and lymphocyte function–associated antigen-1, which promotes the sequestration of activated peripheral T cells into the liver, thereby reducing T cell distribution abnormalities [12]. Additionally, liver-infiltrating myeloid cells in metastatic lesions induce T cell apoptosis via the Fas-FasL pathway, resulting in T cell depletion [13]. This extensive antigen-specific T cell exhaustion drives immunosuppression in preclinical models and cancer patients with liver metastases, leading to the enlargement of metastatic lesions and a poor response to immunotherapy [14].

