### Statistical Analysis

The 2-stage minimax design of Simon was chosen for sample size estimation. With an ORR of 17% or less, HIFU with PD-1 blocking as a combination therapy will be deemed useless or uninteresting; With an ORR of at least 37%, this regimen will warrant further investigation. At a significance level of .05, an analysis with 80% power will require a sample size of at least 30 patients, with 14 during the initial phase and 16 in the next. At the end of the first stage, if 2 or more patients have responded, the second stage can be carried out. If this does not happen, the study has to end. At the end of the study, if at least 8 of 30 patients respond, it will be taken to indicate that the combination therapy is beneficial and worthy of further investigation.

In accordance with the concept of “intention to treat,” all individuals who are given a minimum of 1 injection of the trial medication and undergo effectiveness assessment will be included in efficacy analyses. All patients who are injected with a minimum of 1 dose of the research medication and have a minimum of 1 safety report will be included in the safety analysis. Once we have recorded baseline features, tumor responses, patient-reported outcomes, and adverse events, we will produce descriptive statistics, including Kaplan-Meier survival curves. There will be no data imputation for missing data.

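### PFS is defined as time to progression: death is left out of the event, so a Kaplan-Meier PFS curve that censors such deaths would be too favourable

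*Protocol article*

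**What the plan says.** The End Points section of the protocol article gives PFS a secondary role: "The secondary end points are PFS, OS, disease control rate, safety, and patient-reported outcomes". It then defines the two time-to-event end points in consecutive sentences: "PFS is the length of time between enrollment and the occurrence of disease progression", followed by "OS is the duration between enrollment and death". Death appears in the second definition and not in the first, and no other section adds it to the PFS event.

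For analysis, the Statistical Analysis section says only that "we will produce descriptive statistics, including Kaplan-Meier survival curves". It does not tie these curves to PFS by name and gives no PFS censoring rule.

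On data collection, End Points sets the imaging schedule ("MRI or CT examinations will be administered at the start point, week 3, and each 6 weeks following") and the longer follow-up ("Telephone checks will be conducted every 3 months until the end of the trial, death, or loss to follow-up").

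**The concern.** Progression-free survival is ordinarily read as time to progression or death, whichever comes first. A definition with progression alone is time to progression. The two differ in patients who die before imaging shows progression: these are failures for PFS and non-events for time to progression.

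The stake is a secondary result carrying a name that does not match what was measured. In a single-arm trial there is no control group in which the same omission might partly offset it, so the reported curve and median would be taken at face value as PFS.

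**Working it through.** The article states no PFS median, rate or event count, so there is no figure of its own to reproduce. The check has two parts: the direction, which follows from the definition, and an illustration of size, which rests on assumptions.

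**Direction.** Take a patient who dies at time t without documented progression.
- With death as an event, the Kaplan-Meier curve is multiplied at t by (1 − events/at risk), with this death among the events.
- Under the written definition, with the patient censored at t, the numbers at risk are the same at every time, but there is one event fewer at t. Each factor is therefore equal or larger, and the curve from t onward is higher, or equal if it had already reached zero.

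This needs no assumption about hazards. It does need such patients to be censored, which is the usual treatment of a patient without the event but is not stated in the article. If they were dropped from the curve instead, an upward shift would not follow automatically, but the curve would then describe a group selected by outcome, which is not PFS either.

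**Illustration of size.** Inputs:
- True median PFS, m: not in the article; assumed 4.0 months, with 2 and 6 months for comparison.
- Share d of first events that are deaths without documented progression: not in the article; assumed 5% to 30%.
- Constant hazards: assumed.
- Number of patients: 30 (Statistical Analysis).

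Formulas: the true PFS hazard is ln 2/m. With those deaths censored, the estimated hazard is (1 − d) × ln 2/m. Hence:
- apparent median = m/(1 − d)
- apparent 6-month rate = 0.5^[(6/m)(1 − d)]

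For m = 4.0 the true 6-month rate is 0.5^1.5 = 35.4%.

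| d | Apparent median (months) | Inflation of median | Apparent 6-month rate | Uncounted events if all 30 have one |
|---|---|---|---|---|
| 5% | 4.0/0.95 = 4.21 | 5% | 0.5^1.425 = 37.2% | 1.5 |
| 10% | 4.0/0.90 = 4.44 | 11% | 0.5^1.35 = 39.2% | 3 |
| 20% | 4.0/0.80 = 5.00 | 25% | 0.5^1.2 = 43.5% | 6 |
| 30% | 4.0/0.70 = 5.71 | 43% | 0.5^1.05 = 48.3% | 9 |

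The relative inflation does not depend on m. With d = 30%, a true median of 2 months appears as 2.86 and one of 6 months as 8.57.

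The whole shift comes from the change of event definition. The calculation puts no figure on any further bias that would arise if patients who die were also at higher risk of progression.

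**The case against.** The strongest reply is that this is one line in a condensed article. The label itself contains the word survival, and the full protocol or analysis plan may hold a complete definition. The article also does not say that deaths are censored. Both remarks are fair, and they mean that a biased analysis is not certain. They do not repair the sentence: the article chose to state a definition, it states the wrong event for the label, and the next sentence names death where death is meant.

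The second reply concerns weight, and it stands. PFS is one of several secondary end points, summarised descriptively. No hypothesis, threshold or stopping rule uses it. The two-stage design and its 30 patients rest on the response rate.

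Four stronger readings are tempting, and the document does not support them:
- **That PFS is a principal secondary end point.** It is listed first, but the article gives it no special rank.
- **That the poor survival cited in the Introduction shows a large bias.** For the liver-metastasis subgroup, 3-year survival "was 8%, as compared to a 3-year OS of 17% across all enrolled patients". With a constant hazard, 8% at 36 months is a median survival of about 9.9 months (36 × ln 2/−ln 0.08). That is total mortality, and deaths after progression leave PFS untouched. Imaging at week 3 and then every 6 weeks, and the exclusion of patients with a life expectancy of 3 months or less, argue against a large share of such deaths.
- **That the rule "There will be no data imputation for missing data" makes matters worse.** A recorded death is not a missing value.
- **That the trial's PFS would fail to match the PFS cited in the Introduction.** That section reports only that PFS was shorter with liver metastasis. It gives no value and no definition.

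One limit also remains. The Statistical Analysis section confines efficacy analyses to treated patients who have an effectiveness assessment. Deaths before any assessment may fall outside that set, and a new PFS definition alone would not bring them back.

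**Conclusion.** The point holds as an error in a stated definition: the end point is called PFS and measures time to progression. If patients who die without documented progression are censored, the Kaplan-Meier curve is too favourable whenever such deaths occur. That direction rests on the definition and the censoring alone.

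The size is not known. Inflation of the median by 5% to 43% corresponds to assumed shares of 5% to 30% under constant hazards. Nothing in the article says where in that range the trial would fall, or that it would reach the upper end. A reader might infer that the trial's conclusion on efficacy is at risk. It is not: the response-rate decision is untouched. The definition should nevertheless be corrected before any PFS result is reported.

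**What to change.** Replace the PFS sentence in End Points with: time from enrollment to first documented progression or death from any cause, whichever comes first, with patients alive and progression-free censored at their last adequate tumor assessment. If the full protocol or analysis plan already says this, bring the article's sentence into line with it. If time to progression is also of interest, report it separately under that name, with death treated as a competing event.

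The cost is one sentence. Deaths are already needed for OS and are followed through the telephone checks, so no additional patients, visits or data are required, and the sample size does not change. The Results section gives 6 participants recruited by April 2024 and publication expected in December 2026, which leaves time to settle the definition before analysis. The downside is a shorter reported PFS, by an amount that depends on how many patients die without documented progression.
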